#### *8. Child/adolescent exposure to risks*

Child/adolescent exposure to risks will be evaluated using seven items related to exposure to risky situations. These items have been adapted from those used in evaluations of ParentApp for Teens in Tanzania and

ParentText in South Africa. The items ask about how many times their child has been in any of these situations in the past month. For example, “they were out with friends and ended up walking home alone in the dark”, and “they went to buy food at the market or shop alone at night”. All answers are coded on a frequency scale of 0 to 7, or 8 or more times.

### *9. Online safety*

Online safety will be evaluated using two items adapted from the Global Kids Online: hurtful and bullying behaviour subscale . One item asks, “how many times has your child been gone to meet someone face-to-face that they first got to know on the phone or internet in the past month?” And “how many times has your child brought items home when you didn’t know how they got them?” All answers are coded on a frequency scale of 0 to 7, or 8 or more times.

### *10. Child learning and development*

Child learning and development will be evaluated using six items from the UNICEF Multiple Indicator Cluster Survey (MICS) early childhood development . The items ask about how frequently parents/caregivers spend one on one time with their child, such as “how often in the past week did you read books to or look at picture books with your child?” and “how often in the past week did you tell stories to your child?”. The items will be evaluated on a scale of 0 to 7, or 8 or more times, for frequency. These items will be asked up to age 9.

### *11. Parent support of education*

Parent support of education will be evaluated using five items assessing parent involvement and support for school. These items are based on those used within the Latino Family Study . The items ask about how frequently in the last month the following has happened towards their child, such as “how frequently in the last month you talked about the importance of school and education with your child?” and “how frequently in the last month have you praised your child for working hard at school?”. The items will be evaluated on a 5-point Likert scale of 0 to 4 (0 = Never, 1 = Almost never, 2 = Sometimes, 3 = Often, and 4 = Always).

## Process evaluation outcomes

### *1. Implementation fidelity*

Self-report checklists by facilitators will be used to assess programme implementation fidelity. These checklists include specific activities for each session, such as home practice discussion and coverage of core content. Following that, a ratio of programme implementation to programme design will be created for the self-report scores . According to Borrelli and colleagues, “high treatment fidelity” is defined as a criterion of 80% programme fidelity .

### *2. Programme adherence*

The rates of enrolment, attendance, and dropout will be examined to assess programme adherence. The percentage of parents that participate in the programme will determine enrolment rates. For each ParentChat chat session, parents are considered to have participated if they sent at least one message. The ratio of

sessions attended to total sessions in the programme will be used to calculate the average attendance rates for enrolled participants. The percentage of enrolled participants who fail to attend for at least two consecutive sessions and then fail to attend for any sessions at a later stage will be referred to as the dropout rate.

### *3. Participant satisfaction*

In the post-test assessment, parents and caregivers attending at least one programme session will be asked about their satisfaction with the intervention using five items from a satisfaction questionnaire used in evaluations of PLH-YC in Thailand. Overall participant satisfaction will be calculated in the form of mean and standard deviation values (1 = Very unhelpful; 5 = Very helpful).

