#### **C.1 Study design**

This is a phase II RCT, observer-blinded, with two parallel groups, and designed to evaluate the preliminary effectiveness of ParentChat in reducing child physical and emotional abuse at immediate post-intervention. The study also aims to assess the feasibility and acceptability of the locally adapted version. Randomisation will be performed at the cluster level with a 1:1 allocation ratio.

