### *Blinding*

Blinding will not be possible for those who deliver the programme due to the involvement of facilitators and coaches; additionally, participants cannot be blinded to their allocation status after the initial assessment. In order to reduce the potential of contamination, participants will not be informed of the other participants allocation status. To prevent evaluation bias, participant allocation status will be blinded from data collectors as well as statisticians contributing to data analysis. When blinding is compromised, the Research Manager will be notified as soon as possible to consult with the research team for the most appropriate course of action.

Only in cases where a participant or a member of the research team reports experiencing serious harm as a result of taking part in the study will the unblinding of participants be permitted.

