## **C.2 Outcome data collection**

Data collectors with experience working at the community level with low-income families will be recruited and trained extensively by the study team on ethics, informed consent, and data collection procedures. A detailed protocol will guide data collection to ensure consistency across data collectors. Surveys will be translated into Thai by the researchers and back-translated by an independent translator to ensure accuracy.

Data collection during the trial will take place at four time points. In addition to baseline and one-month post-intervention assessment, which will be done in person, assessments during programme delivery will be conducted telephonically during weeks four, and eight. These assessments will assess changes in target outcomes over the past two weeks.

During pre-post assessments, data collectors will visit participants' homes to complete surveys with them on tablets. Data collectors will sit beside participants and go through the survey together. To reduce the potential for error, data collectors will enter participants' responses into the tablet while showing them the screen. For sensitive sections of the questionnaire (i.e., those relating to IPV and physical/emotional abuse), the tablet is given to the parent, who is able to complete it on their own, using earphones to listen to the questions by audio if they have difficulties with literacy. If parents would prefer to continue completing the survey with the data collector for the sensitive items (as opposed to using CASI), they will continue to use this approach.

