| Child learning and development                       | Multiple Indicator Cluster Survey (MICS)  : early childhood development                                    | Baseline & Post-test | 6         |
| Parent support of education                          | Adapted from those developed for Rosie Ceballo's Latino Family                                             | Baseline & Post-test | 5         |
| Process evaluation outcomes                   |                                                                                                                         |                      |           |
| Implementation fidelity                              | Facilitator checklists                                                                                                  | Post-test            | n/a       |
| Programme adherence                                  | Attendance registration                                                                                                 | Post-test            | n/a       |
| Participant satisfaction                             | Parent/primary caregiver overall satisfaction questionnaire subscale of those used in evaluations of PLH-YC in Thailand | Post-test            | 5         |
| Facilitator and participant engagement               | Process monitoring reports                                                                                              | Post-test            | n/a       |
| Acceptability and feasibility                        | Qualitative interviews                                                                                                  | Post-test            | n/a       |
| Total items at baseline                       |                                                                                                                         |                      | 90 |
| Total items at the fourth and eighth weeks    |                                                                                                                         |                      | 7  |
| Total items at post-test                      |                                                                                                                         |                      | 70 |

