## C.4 Outcome data analysis

Stata 17 will be used for the analysis of general demographic data and the effectiveness of the programme as follows:

Descriptive statistics will be employed to analyse the general demographic data. The average and standard deviation will be used for the continuous data unless that data obviously violates a normal distribution. If the data is obviously a non-normal distribution, the median and interquartile ranges will be used. In addition, frequency and percentage values will be utilised for the categorical data.

All intervention effects will be evaluated utilising an intention-to-treat design, that includes all participants recruited in the study regardless of whether they complete the programme or all the assessment points . To handle missing data, the imputation or deletion method might not be suitable due to the limited sample size. We plan to manage this problem as follows:

- 1) For general demographic information, there is only a measurement time point. Once the data is collected by facilitators before programme delivery, the data will be checked immediately for completion. If any part of the information is found to be incomplete, we will try our best to contact the participants through various channels to request as much information as possible during the period that the participants remain in the programme.
- 2) The missing data in the primary or secondary outcomes will be carried out in the same way as the general demographic. The data will be checked immediately at each time point of the data collection. If any part of the information is found missing, it needs to be followed up on during the time that the participants are still in the project. In the event that the missing data occurs because participants drop out, we will try to contact the participants to find out whether their dropout is related to any factors in the project. If it is evident that there are conflicts or other project-related reasons leading to dropouts, the issues will be addressed to resolve them. If the dropout occurs randomly or it is just a personal reason, the project will go on, and the data will be followed up as much as possible. However, if there are data from at least two time points in each outcome, it is adequate for longitudinal data analysis using multilevel methods, and the missing data does not need to be imputation.

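### Five satisfaction items put only to programme attendees within the collector-run post-test survey disclose the arm of an intervention sub-district to data collectors who are meant to be blinded

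*Protocol*

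**What the plan says.** - **Blinding.** Protocol C.1, Study design: "This is a phase II RCT, observer-blinded, with two parallel groups". The Blinding section gives prevention of evaluation bias as the reason and adds that "participant allocation status will be blinded from data collectors as well as statisticians contributing to data analysis". If blinding breaks, the only provision is to notify the Research Manager.
- **Unit of allocation.** Protocol C.1: "Randomisation will be performed at the cluster level with a 1:1 allocation ratio". Twelve sub-districts are allocated, and each intervention group of 20 comes from one sub-district (Programme delivery). Controls have a LINE group without content or activities (Control condition).
- **Satisfaction items.** Protocol C.3, Participant satisfaction: "In the post-test assessment, parents and caregivers attending at least one programme session will be asked about their satisfaction with the intervention". Table 1 lists them as five items at post-test.
- **Who records the answers.** Protocol C.2, on the baseline and post-test visits: "Data collectors will sit beside participants and go through the survey together". The collector enters the responses. Only the intimate partner violence (IPV) and physical/emotional abuse sections are handed to the parent for self-completion, and the parent may choose to answer those with the collector as well. The Protocol Summary allows a telephone interview when no visit can be arranged.

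**The concern.** Being routed to questions about the programme identifies a participant as belonging to the intervention arm. The collector holding the tablet sees that routing. In an individually randomised trial the leak can be contained by asking such items last, because it then discloses one participant whose outcomes are already recorded. Here the sub-district is the unit of allocation, so one disclosure covers everyone else in it. Placing the items last protects a collector only up to and including the first attendee met in that sub-district.

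At stake is whether post-test outcomes read aloud and entered by a collector are recorded by someone who does not know the arm. The protocol itself sets out to prevent evaluation bias, and its own survey content reopens the route.

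**Working it through.** **1. Are the satisfaction items part of the post-test survey?** Inputs are the item counts in Table 1.

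- Outcome items: child maltreatment 4; positive parenting 2 + 3; parenting stress 1 + 4; corporal punishment 1; child behaviour 14 + 2; depression 7; IPV 7; risk exposure 7; online safety 2; learning and development 6; education support 5.
- Sum: 4 + 5 + 5 + 1 + 16 + 7 + 7 + 7 + 2 + 6 + 5 = 65.
- Baseline: 65 + 23 + 2 demographic and disability items = 90 (stated: 90).
- Weeks four and eight: 4 + 2 + 1 = 7 (stated: 7), with no satisfaction items.
- The row "Total items at post-test" states 70. Without satisfaction the sum is 65; with it, 65 + 5 = 70.

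The stated total is reproduced only if the five items belong to the post-test survey.

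**2. Which answers does the collector enter?** By default the parent self-completes 4 abuse items and 7 IPV items. That leaves up to 65 − 4 − 7 = 54 outcome items entered by the collector, including positive parenting, parenting stress, the child behaviour inventory (CABI), DASS-21 depression and education support. Satisfaction has no self-completion route either.

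**3. How far does one disclosure reach?** The protocol does not state item order, the number of collectors per sub-district or the attendance rate. The figures below therefore rest on assumptions.

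*Upper bound with the items last.* One collector per sub-district, all 20 interviewed, first interviewee an attendee: 20 − 1 = 19 of 20 interviews (95%) follow disclosure. Over six intervention sub-districts this is 6 × 19 = 114 of 240, or 47.5% of the trial.

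*Several collectors.* Take n = 18 interviewed per sub-district (the protocol's 10% attrition applied to 20), everyone attending at least once, the items last, and k collectors who do not tell each other. The share after disclosure is (n − k)/n.

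| Collectors k | Share of an intervention sub-district's interviews |
|---|---|
| 1 | 17/18 = 94% |
| 2 | 16/18 = 89% |
| 4 | 14/18 = 78% |
| 6 | 12/18 = 67% |

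*Low attendance.* If a proportion a attended at least once and a collector does m interviews in the sub-district, the expected share after the first attendee is (1/m) × Σ [1 − (1 − a)^i], for i = 0 to m − 1. With a = 0.5:

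- m = 18: 89%
- m = 9: 78%
- m = 5: (0 + 0.5 + 0.75 + 0.875 + 0.9375)/5 = 61%

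If the items come before the outcome items, the first attendee's own interview is exposed as well.

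**4. Control sub-districts.** An intervention participant who joined no session also skips the items. One interview without them is therefore not decisive, and control status can only be inferred as absences accumulate. This is not quantified here.

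**The case against.** Five points can be made on the other side.

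- **The primary outcome is largely shielded.** The abuse items are self-completed by default, with audio support, and the week-four and week-eight surveys carry no satisfaction items. This stands. A reader might infer that blinding fails for the primary outcome, or that its result is biased. The protocol does not support that: the abuse items are exposed only if the parent prefers to answer with the collector or is interviewed by telephone. Nor does the protocol name a single primary time point.
- **Administration is not fully fixed.** An item total does not say who asks the items or in what order. C.2 mentions a detailed data collection protocol that is not shown, and D.4 speaks of a satisfaction questionnaire. This stands in part. But C.3 places the items in the post-test assessment, and nothing in this protocol assigns them to other staff or to self-completion.
- **The 19-of-20 figure is a bound.** This stands. A reader might take it as 95% of all post-test interviews, but it applies only to intervention sub-districts and under favourable assumptions.
- **Participants know their arm and may mention it anyway.** True, so the change will not guarantee blinding. It does remove a disclosure that the survey itself builds in.
- **Facilitators as data collectors.** C.4 says: "Once the data is collected by facilitators before programme delivery, the data will be checked immediately for completion". A reader might infer that unblinded programme staff collect outcomes. The sentence concerns demographic data gathered before delivery, and the Allocation section randomises only after baseline, so there is no arm to disclose at that point. The later remark that missing outcome data are handled in the same way refers to checking and follow-up and names no facilitator. What remains is a wording mismatch with the Protocol Summary and C.2, which assign collection to data collectors.

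**Conclusion.** The contradiction holds. C.1 promises blinded data collectors, while C.3, C.2 and Table 1 together have those collectors administer items that only intervention attendees receive. With allocation by sub-district, certain disclosure can precede up to 19 of 20 interviews in an intervention sub-district (114 of 240 across the trial) if the items come last. In the illustrative scenarios the share within an intervention sub-district runs from about 61% to 94%. These shares depend on item order, collector numbers, attendance and collectors not sharing what they learn, none of which the protocol states.

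The finding concerns the blinding claim at post-test, mainly for collector-entered proximal and secondary outcomes. It does not establish the size or direction of any bias. Survey content and blinding are both set in this protocol, so the matter cannot simply be left to an analysis plan. The change is cheap and worth making.

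**What to change.** Remove the five satisfaction items from the post-test outcome survey, so that both arms receive the same 65 items. Give the satisfaction items separately after all outcome interviews in that sub-district are complete, for example through a LINE or ODK link, with audio support for caregivers who have difficulty reading. Amend C.3 and the Table 1 post-test total to match. If the items must stay in the visit, state in C.1 that collectors are not reliably blinded at post-test.

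As a separate wording correction, bring the reference to facilitators in C.4 into line with the Protocol Summary and C.2.

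The cost is a slightly lower response to the satisfaction items and one extra contact. The sample size of 240 does not change.

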### *4. Facilitator and participant engagement*

The level of engagement will be determined by the number, type, and word count of messages that facilitators and participants send to the online groups during each session. Additionally, the number of activities completed by each participant (such as home assignments) will be used as a measure. Message logs will be exported into a secure database and pseudo-anonymised messages prior to sharing with local research team. The researcher will conduct a content or narrative analysis of text messages to evaluate the acceptability of programme content, quality of programme delivery, and interactions and communication patterns between facilitators and participants. A summary of the challenges or issues found regarding participant and facilitator engagement will be included in the weekly assessment.

### *5. Acceptability and feasibility*

After the programme, a focus group discussion (FGD) with the facilitators (n = 6) and individual interviews with programme participants (n = 12) will be conducted to assess programme acceptability and feasibility. The inclusion criterion for participation in individual interviews will be attendance at least one session. Participants will be purposefully selected using the following criteria: high engagement (n = 4), low engagement (n = 4), and dropouts (n = 4). Additionally, the participant's sex will be taken into consideration in the selection criteria. Four to six fathers or male caregivers will be invited to participate in the individual interviews for the male engagement. All parent interviews will be conducted by trained researchers. The participant interviews will be conducted in person in the participants' homes for about 60 minutes, or they may be conducted over the phone if the participants are unable to do in person interviews. The interview will be audio recorded, and notes will also be taken in case the recording doesn't work. The FGD will be both audio and video recorded, and written notes will be taken as back up. The FGD will take between 60 and 90 minutes and will be conducted in person at the health promoting hospital or at the Boromarajonani College of Nursing, Udon Thani.

The focus group and interviews will be conducted during the post-evaluation with the following themes:

- Participants' observed change in parent-child relationships at home during programme;
- Cultural acceptability and appropriateness of programme delivery, and key programme components;
- and

- Existing barriers to participation during sessions and engagement in home practice and other activities.

The FGD will also focus on the benefits to the programme (in terms of content, logistics, and process), problems faced by facilitators during programme delivering on both a logistical level (such as recruiting, session length, and online delivery format) and process (such as using a collaborative approach and/or explaining concepts such as child-led play).

Following the feedback on acceptability and feasibility expressed by participants, all interviews and FGD records will be transcribed using computer programmes such as NVivo to organise the information. Thematic analysis  will be used to analyse the data. The researchers will evaluate and code the transcripts. The codes will be defined into the following themes: 1) overall experience; 2) cultural and contextual relevance of programme themes and skills, structure, schedule, and logistics; 4) barriers and facilitators of programme participation, engagement, and implementation; and 5) possibility of programme scale-up. This is also looking for which themes emerge from the data. The validity and representativeness of each theme will be emphasised during the research team's discussion of the findings. Lastly, we will choose a few data extracts that highlight important themes and opposing perspectives.

